## Abstract

**Background:**

Anthracyclines, alone or in combination with other drugs, are among the most effective chemotherapeutic agents to treat breast cancer both in the adjuvant and neoadjuvant setting. Unfortunately, anthracycline-associated dose-dependent cardiotoxicity is a limiting factor in clinical use. Extensive efforts have been devoted to identifying strategies to prevent anthracycline-induced cardiotoxicity. However, most cardioprotective agents have shown little effect in clinical trials. Herbal medicines are pure, natural substances that have been used for centuries in many countries, including China. This trial aims to evaluate the cardioprotective effects and safety of *Platycodon grandiflorum* granules compared to placebo granules in patients with early breast cancer receiving anthracycline-based chemotherapy.

**Method/design:**

This study is a single-center, double-blinded, randomized, placebo-controlled, parallel-group trial. A total of 120 patients will be randomly allocated in a 1:1 ratio to receive either *P. grandiflorum* granules or placebo granules twice daily for 12 weeks. The primary outcome is heart failure (either clinical or subclinical). The secondary outcomes include all-cause mortality, cardiac death, electrocardiogram (ECG) findings, left ventricular diastolic function, longitudinal systolic strain and velocities measured by tissue Doppler imaging, cardiac biomarkers, such as troponin I (TnI), brain natriuretic peptide (BNP), and creatine kinase isoenzymes (CK-MB). Assessments will be performed at baseline (before randomization) and 3, 6, 9, 12, 16, and 20 weeks after randomization.

**Discussion:**

This will be the first clinical trial to evaluate the cardioprotective effects and safety of *P. grandiflorum* in patients with early breast cancer receiving anthracycline-based chemotherapy. We are also performing this trial to assess the feasibility of a larger-scale clinical trial in the future.

**Trail registration:**

Chinese Clinical Trial Registry, ChiCTR-IPR-16009256. ﻿Registered on 23 September 2016.

**Electronic supplementary material:**

The online version of this article (doi:10.1186/s13063-017-2140-z) contains supplementary material, which is available to authorized users.

## Background

Anthracycline (ANT) compounds (e.g., doxorubicin (DOX), epirubicin (EPI), and daunorubicin (DNR)) are some of the most effective antineoplastic drugs in the treatment of both hematological malignancies and solid tumors [1]. Moreover, anthracycline-based treatments are first-line chemotherapy agents to treat early breast cancer [2]. Unfortunately, the clinical use of anthracyclines is limited in some patients by the risk of severe cardiotoxicity, especially in patients receiving high cumulative drug doses [3].

Cardiac complications after DNR exposure were first reported in 1967 [4]. Since then, accumulating evidence has deemed cardiotoxicity a side effect common to all ANTs. Despite almost 50 years of efforts to prevent anthracycline-induced cardiotoxicity, there still remains considerable controversy regarding the best way to do so. Various potential cardioprotective agents, including dexrazoxane, coenzyme Q10, vitamin E, angiotensin converting enzyme (ACE) inhibitors, statins, and beta blockers, have been well-studied to determine their cardioprotective effects [5–10]. A Cochrane systematic review concluded that the only agent to have a cardioprotective effect was dexrazoxane (risk ratio (RR) 0.18, 95% confidence interval (CI) 0.10–0.32, *P* < 0.00001) [11]. But dexrazoxane is only approved by the US Food and Drug Administration (FDA) for women with metastatic breast cancer who havereceived at least 300 mg/m^2^ doxorubicin and need additional doxorubicin to maintain tumor control. Additionally, dexrazoxane is not widely used even for this indication due to cost, especially in developing countries [12]. Moreover, dexrazoxane is not without its own side effects, including the potential increased risk of secondary malignancy [13].

In the absence of effective, affordable therapies, some physicians in China turn to alternative or complementary treatments to prevent anthracycline-induced cardiotoxicity. Chinese herbal medicine (CHM) is an essential part of traditional Chinese medicine (TCM), and has been widely used in China for centuries. According to TCM theory, patients with anthracycline-induced cardiotoxicity are diagnosed as “Xiong bi.” “Qi deficiency” is the major syndrome. *Platycodon grandiflorum* (*jiegeng*) is an herb that has been used in TCM for thousands of years to treat cardiovascular disease. In TCM theory, *P. grandiflorum* can nourish Qi and relieve symptoms, such as palpitations, shortness of breath, and chest pain.

The molecular basis for cardiotoxicity after ANT exposure remains unclear. The most widely accepted hypothesis for anthracycline-induced cardiotoxicity is the generation of excess reactive oxygen species (ROS) and redox cycling [14]. However, a series of in vitro and in vivo studies investigating treatment with antioxidants or iron chelation agents failed to prevent cardiac toxicity caused by doxorubicin [15, 16]. Some studies found that extract from *P. grandiflorum* has stronger antioxidant effects than conventional antioxidants. *P. grandiflorum* can reduce formation of ROS and lipid peroxidation [17, 18]. Additional studies found that too much or too little nitric oxide (NO) might damage myocardial cells, and *P. grandiflorum* can maintain the concentration of NO in myocardial cells [19–22].

Therefore, *P. grandiflorum* may have the potential to prevent anthracycline-induced cardiotoxicity. Compared with dexrazoxane, *P. grandiflorum* has the advantage of being more affordable. However, there have been no high-quality clinical trials that evaluate the safety and efficacy of *P. grandiflorum*. This study aims to evaluate the cardioprotective effects and safety of *P. grandiflorum* compared to placebo in patients with early breast cancer receiving anthracycline-based chemotherapy. This trial was also performed to assess the feasibility of a large-scale clinical trial that may provide alternative, evidence-based prevention of anthracycline-induced cardiotoxicity.

## Methods/design

### Study objective

The primary objective of this study is to ascertain the potential cardioprotective effects and safety of *P. grandiflorum* compared to placebo in patients with early breast cancer receiving anthracycline-based chemotherapy. The secondary objective is to determine whether there are other possible effects of *P. grandiflorum* on protecting against other, non-cardiac anthracycline toxicities.

### Hypothesis

We hypothesize that: (1) after 12 weeks, fewer patients taking *P. grandiflorum* will develop cardiac damage compared with patients receiving placebo, (2) *P. grandiflorum* will be safe at the dosage used in this trial, and (3) *P. grandiflorum* will have similar effects to placebo on non-cardiac anthracycline toxicities.

### Study design

This is a single-center, double-blinded, randomized, placebo-controlled, parallel-group trial. Figure 1 depicts a flow chart of the study. A Standard Protocol Items: Recommendations for Interventional Trials (SPIRIT) checklist for this protocol is also provided (see Additional file 1).

**Fig. 1 Fig1:**
[figure not shown]
Flow chart of the study

### Recruitment

The study will be performed in the Breast Surgery Unit (Integrated Traditional Chinese and Western Medicine) of Longhua Hospital affiliated with Shanghai University of Traditional Chinese Medicine. The study will identify patients diagnosed with early breast cancer at our center who are receiving anthracycline-based chemotherapy. Patients receiving either adjuvant or neoadjuvant chemotherapy will be recruited. Participants who initially present to our hospital through both inpatient and outpatient units will be screened. Eligible patients who agree to participate will be asked to sign an informed consent form. To achieve adequate participant enrollment, study drug will be provided to participants at no cost. No other financial incentives will be provided to either treating physicians or patients.

### Eligibility criteria

#### Inclusion criteria

Patients will be eligible for inclusion if they meet all of the following criteria:Histological or cytological proven breast cancerReceiving anthracycline-based chemotherapyKarnofsky Performance Status (KPS) ≥ 60Life expectancy ≥ 6 monthsAged 20–70 yearsWilling and able to give informed consent

#### Exclusion criteria

Patients will be excluded if any of the following occurs:History of myocardial injury, coronary artery disease (CAD), myocarditis, or functional cardiac insufficiencyPrevious anthracycline-based chemotherapy or radiotherapyPrevious treatment with any investigational drug within 3 months prior to receiving the first dose of *P. grandiflorum* (or placebo)Metastatic diseasePregnancyLack of complianceAllergic to investigational drugsParticipation in other clinical trial(s) within 3 months prior to this trial

### Randomization, allocation concealment, and blinding

To minimize selection bias, all eligible patients will be randomized in a 1:1 ratio to the treatment group or control group. We will use IBM SPSS software version 19 (IBM, Armonk, NY, USA) for group allocation according to a randomization list. Randomization will be performed by a professional, independent statistician who is not involved in the recruitment process of the study. The randomization codes will be concealed in sequentially prepared, coded, individual, opaque envelopes prepared by research assistants who are not involved in the recruitment process. The envelopes will be kept secure in the Good Clinical Practice (GCP) Centre of Longhua Hospital and will not be opened until after statistical analysis or in the case of a medical emergency. The study participants, study investigators, other research team members, pharmacists, nurses, and technicians will remain blinded to the allocation of study medication versus placebo.

### Study drug

CHM extract granules have been used in China for many years. In this study, the *P. grandiflorum* and placebo granules used were both manufactured by Jiangyin Tianjiang Pharmaceutical Co., Ltd (Jiangyin, China), a manufacturer of CHM extract granules that has been certified for Good Manufacturing Practice. *P. grandiflorum* granules have been approved by the China Food and Drug Administration (CFDA). Quality control was conducted by the company. *P. grandiflorum* granules contain a single herb, *P. grandiflorum*. A raw *P. grandiflorum* herb weighing 3 g was cooked in boiling water. The residual was then filtered, concentrated, spray-dried, and mixed with starch and sucralose. Finally, the *P. grandiflorum* granules were packaged in small pouches weighing 2 g each. The placebo granules are composed of 10% *P. grandiflorum* (a sub-therapeutic dose) and 90% starch, giving the placebo an identical appearance, smell, taste, and packaging as the *P. grandiflorum* granules.

### Intervention

Enrolled patients will be randomly allocated to either the treatment or control group. Patients in the treatment group will receive anthracycline-based chemotherapy with *P. grandiflorum* granules. Patients in the control group will receive anthracycline-based chemotherapy with placebo granules. All patients, regardless of which group they are randomized to, will be instructed to dissolve one package of granules in 150 mL hot water twice daily for 12 consecutive weeks. Participants will be withdrawn if they take any other CHM or Western medication to treat heart disease during the 12-week intervention period or if they are not willing to take the study drug. Treatment for other conditions, such as hypertension, diabetes mellitus, and other chronic diseases, will be permitted during the intervention. The name, duration, and dosage of any other drugs taken during the 12-week intervention period will be recorded in each patient’s case report form (CRF). In order to assess adherence to taking the intervention medication, each participant will be asked to undergo laboratory tests at each follow-up appointment. Patients will also be asked to return any unused drug granules. Participants who return more than 10% of the total allotted granules will be defined as nonadherent. Patient-reported reasons for nonadherence will be recorded on the CRF.

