### Outcomes

#### Primary outcome

The primary outcome is heart failure (either clinical or subclinical). In this study, New York Heart Association (NYHA) Functional Classification will be used to evaluate the extent of clinical heart failure. Left ventricular ejection fraction (LVEF) less than 50% or a drop of more than 15% from baseline is defined as subclinical heart failure in this study. Ejection fraction is measured using multigated acquisition (MUGA) scan in all participants. MUGA scans will be performed by the same physician; this physician is not involved in recruitment of the study.

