### Sample size calculation

The study aims to detect the cardioprotective effects of *P. grandiflorum* in patients with early breast cancer receiving anthracycline-based chemotherapy. Sample size was calculated on the basis of the primary outcome. Since no randomized controlled trials (RCTs) have been previously performed on the cardioprotective effects of *P. grandiflorum* in patients receiving anthracycline-based chemotherapy, we proposed this study to evaluate the feasibility of a large-scale clinical trial. Anticipating a 20% dropout rate, a total of 120 patients, with 60 patients in each group, will be recruited for the pilot study.

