### Statistical analysis

An independent, professional statistician will perform the data analysis for the results and the AEs. Intention-to-treat (ITT) analysis will be carried out in all participants who complete the clinical trial. Missing data will be adjusted for using the last observation carried forward (LOCF) principle to obtain a complete database. Continuous data will be presented as means and standard deviations $$ \left(\overline{X}\pm SD\right) $$, or medians and quartiles. The comparability of the two groups will be assessed using the independent samples *t* test for continuous variables and the chi-square (χ^2^) test or Wilcoxon test, when appropriate, for categorical variables. The cumulative dose of anthracycline to cause cardiotoxicity will be estimated in each group using Kaplan-Meier curves; differences between the curves will be assessed using the log-rank method. The crude and adjusted hazard ratios and 95% confidence intervals will be estimated using a Cox proportional hazards regression model. All analyses will be performed using IBM SPSS software version 19 (IBM, Armonk, NY, USA). A two-tailed *P* value <0.05 was set for statistical significance.

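### Withdrawing patients who take heart-disease medication, combined with a completers-only analysis, can remove primary heart-failure events from the trial because they occurred and were treated

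*Protocol article*

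**What the plan says.** Three sections of the protocol article bear on this.

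- **Intervention:** "Participants will be withdrawn if they take any other CHM or Western medication to treat heart disease during the 12-week intervention period". The same sentence withdraws participants who are unwilling to take the study drug. The next one allows other treatment: "Treatment for other conditions, such as hypertension, diabetes mellitus, and other chronic diseases, will be permitted during the intervention".
- **Primary outcome:** the outcome is heart failure, clinical (graded by NYHA class) or subclinical. For the latter, "Left ventricular ejection fraction (LVEF) less than 50% or a drop of more than 15% from baseline is defined as subclinical heart failure".
- **Statistical analysis:** "Intention-to-treat (ITT) analysis will be carried out in all participants who complete the clinical trial". This is followed by "Missing data will be adjusted for using the last observation carried forward (LOCF) principle to obtain a complete database". The same section plans Kaplan-Meier curves, a log-rank test and Cox hazard ratios.

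On follow-up, the abstract states: "Assessments will be performed at baseline (before randomization) and 3, 6, 9, 12, 16, and 20 weeks after randomization". The exclusion criteria remove patients with prior myocardial injury, coronary artery disease, myocarditis or cardiac insufficiency. No section says that withdrawn participants continue their assessments, or that starting heart medication counts as an event.

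**The concern.** The withdrawal rule is triggered by something the primary outcome can cause. Because patients with existing cardiac disease are excluded, heart-disease medication started on study will mostly be a response to new cardiac disease, including the condition the trial is meant to count. A patient who develops heart failure and is treated for it within 12 weeks is withdrawn, is then not a completer, and so falls outside the analysis set as worded.

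The consequence depends on how such a patient is handled, and the two possibilities should be kept apart.

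- If the patient is **excluded**, the event is lost, and observed risks and power fall.
- If the patient is instead kept but **censored** before an event is recorded, the censoring is informative, because the reason for it is the outcome process.

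In either case, data that are not collected after withdrawal cannot be recovered at analysis. The same patients may also be lost to the mortality and cardiac-death outcomes. The article presents the trial as preparation for a larger one, so distorted event rates would carry over into that trial's planning.

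**Working it through.** **The plan's own figure.** "Anticipating a 20% dropout rate, a total of 120 patients, with 60 patients in each group, will be recruited for the pilot study". Only the dropout step can be checked: 60 × (1 − 0.20) = 48 evaluable per arm, and 48 / 0.80 = 60. No event rate, effect size or power is given, so 120 itself cannot be reproduced, and the risks below are assumptions.

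**Model for exclusion.** Let p be the true risk in an arm and w the share of cases withdrawn and left out. The observed risk among those who remain is

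p(1 − w) / (1 − pw).

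The number remaining is 60 × (1 − pw). Power is the normal approximation for two proportions at two-sided 0.05, the level the article sets, with no other dropout.

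**Equal loss in both arms, assumed true risks 30% control and 15% treatment.** For w = 0.5: control 0.15/0.85 = 17.6%, treatment 0.075/0.925 = 8.1%, with 51 and 55.5 patients remaining.

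| Share of cases lost | Control | Treatment | Risk difference (points) | Risk ratio | Power |
|---|---|---|---|---|---|
| 0% | 30.0% | 15.0% | 15.0 | 0.50 | 50% |
| 25% | 24.3% | 11.7% | 12.6 | 0.48 | 42% |
| 50% | 17.6% | 8.1% | 9.5 | 0.46 | 32% |
| 75% | 9.7% | 4.2% | 5.5 | 0.44 | 19% |

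With 20% against 10%, the same shares take the risk difference from 10.0 to 8.1, 5.8 and 3.2 points and power from 33% to 27%, 20% and 13%. With 25% against 12.5% and w = 0.5, observed risks are 14.3% and 6.7%, so the difference falls from 12.5 to 7.6 points.

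**Relative effect under equal loss.** The observed odds are p(1 − w)/(1 − p), which is the true odds times (1 − w). The same factor applies in both arms, so the odds ratio does not change: for 30% against 15% it is 0.176/0.429 = 0.41 at every w. The risk ratio drifts slightly away from 1.

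**Unequal loss, no true effect (30% in both arms).** Losing 25% of cases gives 0.225/0.925 = 24.32%; losing 50% gives 0.15/0.85 = 17.65%.

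- 25% lost in control, 50% in treatment: 0.1765/0.2432 = 0.73, an apparent benefit.
- Reversed: 0.2432/0.1765 = 1.38, an apparent harm.

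**Unequal loss, true risks 30% and 15% (true risk ratio 0.50).**

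- 50% lost in control, 25% in treatment: 17.6% against 11.7%, risk ratio 0.66, power 14%.
- 25% lost in control, 50% in treatment: 24.3% against 8.1%, risk ratio 0.33, power 64%.

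**The case against.** The strongest reply has four parts.

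1. **The mechanism is narrower than it first looks.** A reader might infer that every heart-failure case is removed. The text does not support that. The trigger is taking medication, not having heart failure, so untreated cases stay in. Subclinical failure is defined by an LVEF result, and that event normally exists before any treatment it prompts. The rule runs for 12 weeks, while assessments run to week 20. How often LVEF is measured is left to Fig. 2, so how many events would go unrecorded before treatment cannot be judged from the text. All of this stands and limits the size.

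2. **A real benefit need not shrink.** A reader might infer that the rule always pulls the result towards no effect. Under equal loss this is true of the risk difference only. The article plans hazard ratios, and the risk and odds ratios above hardly move. This stands: bias in a relative measure needs unequal loss, and its direction is then open.

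3. **The wording is ambiguous.** Withdrawal could mean from study drug only, and carrying observations forward to complete the database suggests that some incomplete patients are kept. This stands only in part. The sentence speaks of participants, and for those who already refuse the granules, withdrawal from granules alone would add nothing. The analysis set is expressly limited to completers. Even if LOCF were applied, a patient treated between visits could carry forward a pre-event value and be scored as event-free.

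4. **It overlaps with the completers-only sentence.** Correcting that sentence would bring back events already recorded. It would not bring back events that go unrecorded because follow-up stopped, so the withdrawal rule needs its own correction.

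**Conclusion.** The concern holds in this form: followed as written, the three sections allow patients who develop the primary outcome in weeks 0 to 12, and are treated for it, to leave follow-up and the primary analysis because of it. This rests on explicit text and not on detail that a condensed article would be expected to omit.

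The size is unknown. It depends on event rates that the article does not give and on the share of cases treated within 12 weeks, which is assumed here at 25% to 75%. Over that range, with 30% against 15% true risk and equal loss, power falls from 50% to between 42% and 19%, and the risk difference from 15.0 to between 12.6 and 5.5 points, with the relative effect nearly unchanged. With unequal loss the relative effect is biased in either direction.

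The documents do not support saying that all cases are lost, that a benefit must be diluted, or that the same patients are both excluded and censored. The exclusion and censoring consequences are alternatives, and the article does not make clear which applies.

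**What to change.** Reconcile the Intervention, Primary outcome and Statistical analysis sections as follows.

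- Separate stopping the study granules from withdrawal from the trial.
- Keep participants who start heart-disease medication or stop granules in the assessments already scheduled to week 20, unless they withdraw consent.
- Analyse all randomised participants in their allocated group, and drop the restriction to completers.
- Count primary events recorded before or after the medication starts.
- Add a sensitivity analysis in which new heart-failure medication counts as an event.

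Which medicines are permitted and when granules stop remain the sponsor's decisions; nothing here requires those rules to change.

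The cost is mainly protocol wording. The visits are already planned and no unscheduled scan is needed. The article reports that recruitment was ongoing, so the change would have to be made during the trial and would protect only participants still in follow-up or yet to enrol. The small downside is that some LVEF values after medication starts, including some before week 12, would be measured on heart medication. Recording the start date, which the case report form already covers for drugs taken in the 12-week period, lets the analysis show how many values are affected.

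### As worded, a patient treated for heart failure in weeks 0-12 is withdrawn and may drop out of the analysis of heart failure, the primary outcome

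*Protocol article*

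**What the plan says.** All references are to the protocol article.

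- **Intervention.** "Participants will be withdrawn if they take any other CHM or Western medication to treat heart disease during the 12-week intervention period". No exception is made for someone who has just reached the primary outcome. The rule is limited to the 12 weeks of treatment, and the same section permits treatment of hypertension, diabetes and other chronic diseases. It also requires a drug record: "The name, duration, and dosage of any other drugs taken during the 12-week intervention period will be recorded".
- **Primary outcome.** "The primary outcome is heart failure (either clinical or subclinical"). Clinical heart failure is graded by NYHA class. Subclinical heart failure is an LVEF below 50% or a fall of more than 15% from baseline.
- **Exclusion criteria.** Patients with a history of "myocardial injury, coronary artery disease (CAD), myocarditis, or functional cardiac" insufficiency are not enrolled.
- **Statistical analysis.** The population: "Intention-to-treat (ITT) analysis will be carried out in all participants who complete the clinical trial". Missing data: "Missing data will be adjusted for using the last observation carried forward (LOCF) principle". Event analysis: "The cumulative dose of anthracycline to cause cardiotoxicity will be estimated in each group using Kaplan-Meier curves", with a log-rank test and a Cox model.
- **Abstract, Method/design.** Assessments are at baseline and weeks 3, 6, 9, 12, 16 and 20. Four post-baseline visits fall inside the withdrawal window and two after it.

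**The concern.** Drugs for heart failure are drugs for heart disease. Because most prior cardiac disease is excluded at entry, at least some heart-disease medication started in the first 12 weeks will be treatment of the outcome itself. Taken together, the withdrawal rule and the completer population then make membership of the analysed set depend on the outcome, and that set no longer reflects the groups that were randomised.

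At stake are events, which are likely to be few in a trial of 120, and the validity of the comparison if the two arms lose different shares of their events. The article states both the rule and the population, so this is not detail left to an analysis plan. A later plan could redefine the population, but it could not recover visits that were never made because participation ended.

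**Working it through.** **1. What happens to a patient who starts heart-failure treatment in weeks 0-12**

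| Reading of the Statistical analysis section | Event recorded before the drug start | Threshold not yet met at the drug start |
|---|---|---|
| Completers only (plain wording) | Patient dropped, event lost | Patient dropped |
| Kept, LOCF | Event kept | Carried forward as a non-event |
| Kept, Kaplan-Meier/Cox | Event kept | Censored at withdrawal, informatively |
| Visits continue and patient counts as a completer | Event kept | Later event observed |

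The second column of outcomes is realistic because ECG, troponin I and BNP are also measured (Secondary outcomes) and could prompt treatment before LVEF crosses the threshold.

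**2. The plan's own figure**

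The 120 cannot be rebuilt, because no event rate, effect or power is stated. Only the dropout step can be checked: 48/(1 - 0.20) = 60 per arm is consistent, but 48 does not appear in the article.

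**3. Illustration**

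From the article: 60 per arm, two-sided 0.05. Assumed: control risk 10-30%, true risk ratio 0.50 (or 1.00), and a share w of 10-30% of would-be events lost.

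For true risk p, the observed risk is:
- LOCF, lost before the threshold: p(1 - w)
- Completers: p(1 - w)/(1 - pw)
- Kaplan-Meier: events spread evenly over the six visits, lost cases censored just before their event visit. Visits stand in for the cumulative-dose axis, and losses are allowed at all six although the rule reaches only four. With events spread evenly, 10-30% of all events is 0.10/(4/6) = 15% to 0.30/(4/6) = 45% of those in the window.

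*Equal shares, 30% v 15%.* Expected events without loss: 60 × 0.30 + 60 × 0.15 = 18 + 9 = 27.
- w = 0.10: 16.2 + 8.1 = 24.3
- w = 0.30: 12.6 + 6.3 = 18.9
- Patients lost: control 18 × 0.10 to 0.30 = 1.8-5.4; treatment 9 × 0.10 to 0.30 = 0.9-2.7

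| | w = 0 | w = 0.10 | w = 0.30 |
|---|---|---|---|
| Risk ratio, LOCF | 0.500 | 0.500 | 0.500 |
| Risk ratio, Kaplan-Meier | 0.500 | 0.495 | 0.485 |
| Risk ratio, completers | 0.500 | 0.492 | 0.476 |
| Power, LOCF | 50.3% | 45.2% | 35.0% |
| Power, completers | 50.3% | 47.1% | 39.9% |

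Power is for a two-proportion z test. Worked example, completers at w = 0.10: 0.27/0.97 = 0.278 and 0.135/0.985 = 0.137, ratio 0.492.

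At 20% control risk, 18 events fall to 16.2-12.6. At 10%, 9 fall to 8.1-6.3.

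*Unequal shares, control risk 30%* (LOCF / Kaplan-Meier / completers):

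| Lost in control / treatment | True 0.50 reads | True 1.00 reads |
|---|---|---|
| 20% / 10% | 0.563 / 0.546 / 0.537 | 1.125 / 1.103 / 1.090 |
| 10% / 20% | 0.444 / 0.444 / 0.444 | 0.889 / 0.906 / 0.917 |

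If no heart drug is started around an event, w = 0 and nothing changes.

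**The case against.** The strongest reply is that the text does not establish the loss. Neither withdrawal nor completion is defined. Withdrawal might mean stopping the granules only, and the intention-to-treat label, LOCF and Kaplan-Meier/Cox methods all normally keep people with partial follow-up. A reader might infer that every treated patient necessarily leaves the analysis; the article does not support that. If visits continue and the patient counts as a completer, nothing is lost. What stands is that the completer sentence says the opposite of those methods, and nothing in the article resolves the conflict.

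The affected group is also narrow. The rule stops at week 12, hypertension treatment is allowed, and a subclinical event triggers withdrawal only if a heart drug follows, which nothing requires. A drug started because of a scheduled LVEF result follows an event already recorded, and correcting the completer sentence alone would keep that event. All of this stands. The withdrawal rule still matters for patients treated before the threshold is met.

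A reader might also infer that the rule favours one arm. Participants and staff "will remain blinded to the allocation of study medication versus placebo", so equal shares are the base case, and the risk ratio then barely moves. What remains is lost power in a study called a pilot, with no stated power target. That limits the importance, although the Statistical analysis section still sets a two-sided 0.05 significance level.

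Finally, the rule plausibly limits contamination: the Background lists ACE inhibitors, beta blockers and statins as candidate cardioprotectants. That is a reason to record such drugs and report them by arm. It is not a reason to discard patients who have the outcome.

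**Conclusion.** The concern holds in a limited form. As written, the withdrawal rule and the completer population together may remove a patient treated for heart failure in weeks 0-12 even when the event is on record. If the patient is kept, an event not yet at the threshold when treatment starts becomes a carried-forward non-event or an informative censoring.

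The true size is unknown, since event rate, effect and share lost are all assumptions here. In the blinded base case the cost is events and power: 27 events to 24.3-18.9 and power from 50% to 35-47% at 30% v 15%, and only 9 events to 8.1-6.3 at 10% control risk. Material bias needs unequal shares. It could then go either way, and the article gives no basis for saying which. The change is worth making, with medium confidence that the loss would occur in practice.

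**What to change.** 1. **Intervention.** Replace withdrawal for heart-disease medication with: the patient may stop the granules if clinically needed but continues all scheduled assessments to week 20.
2. **Statistical analysis.** Replace the completer population with all randomised patients as allocated. Count every recorded primary-outcome event before or after the drug start, and do not censor at the drug start in Kaplan-Meier or Cox. For patients already withdrawn, keep their recorded events.
3. **Reporting.** Give cardiac-drug starts by arm from the drug record already required.
4. **Optional sensitivity analysis.** Count a drug newly started for heart failure or cardiac dysfunction as an event. Do not count every heart-disease drug, because that would label other conditions as heart failure.

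The cost is one amendment while recruitment is ongoing (Trial status), plus already-scheduled visits for a few patients: about 2-5 control and 1-3 treatment at the assumed 30% v 15%. The downside is that the main estimate then includes the effect of rescue cardiac treatment on later LVEF. The sensitivity analysis does not measure that effect; it only shows the result when starting such a drug is itself an event.
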